## Abstract

**Background:**

The MyPeBS study is an ongoing randomised controlled trial testing whether a risk-stratified breast cancer screening strategy is non-inferior, or eventually superior, to standard age-based screening at reducing incidence of stage 2 or more cancers. This large European Commission-funded initiative aims to include 85,000 women aged 40 to 70 years, without prior breast cancer and not previously identified at high risk in six countries (Belgium, France, Italy, Israel, Spain, UK). A specific work package within MyPeBS examines psychological, socio-economic and ethical aspects of this new screening strategy. It compares women’s reported data and outcomes in both trial arms on the following issues: general anxiety, cancer-related worry, understanding of breast cancer screening strategy and information-seeking behaviour, socio-demographic and economic characteristics, quality of life, risk perception, intention to change health-related behaviours, satisfaction with the trial.

**Methods:**

At inclusion, 3-months, 1-year and 4-years, each woman participating in MyPeBS is asked to fill online questionnaires. Descriptive statistics, bivariate analyses, subgroup comparisons and analysis of variations over time will be performed with appropriate tests to assess differences between arms. Multivariate regression models will allow modelling of different patient reported data and outcomes such as comprehension of the information provided, general anxiety or cancer worry, and information seeking behaviour. In addition, a qualitative study (48 semi-structured interviews conducted in France and in the UK with women randomised in the risk-stratified arm), will help further understand participants’ acceptability and comprehension of the trial, and their experience of risk assessment.

**Discussion:**

Beyond the scientific and medical objectives of this clinical study, it is critical to acknowledge the consequences of such a paradigm shift for women. Indeed, introducing a risk-based screening relying on individual biological differences also implies addressing non-biological differences (e.g. social status or health literacy) from an ethical perspective, to ensure equal access to healthcare. The results of the present study will facilitate making recommendations on implementation at the end of the trial to accompany any potential change in screening strategy.

**Supplementary Information:**

The online version contains supplementary material available at 10.1186/s12885-022-09484-6.

## Background

Breast cancer is the leading cause of death among women worldwide [1]. Breast screening programmes use age as the primary criterion for eligibility and primarily target women over 50 years of age.^1^ Across countries, numerous scientific and medical debates exist on the optimal screening interval, and on whether younger women would also benefit from screening programmes. The discussions focus on the need to improve the balance of benefits of mammographic screening relative to potential harms including false-positive and false-negative findings, over diagnosis, over treatment, and the associated anxiety and unnecessary costs [2–4]. Recent reviews of the evidence on breast cancer screening found clear support that screening prevents early deaths, but also made such harms apparent and suggested more flexible strategies may help [5, 6].

Since the risk of developing breast cancer varies widely among women (according to age, genetics, family history, history of benign breast disease, BMI, hormone and other exposures, etc.), risk-based approaches to breast cancer screening have recently emerged as promising cancer prevention strategies [7–9]. These require applying risk assessment to the whole screening population, stratifying the population into several risk groups, assigning individuals to a risk group, and tailoring prevention and early detection interventions to each risk group [10]. Potential benefits of risk stratified screening for women identified as being at higher risk could include increased awareness, more frequent and sensitive screening, and being offered interventions that can reduce their risk [11]. Internationally, there are several ongoing trials analysing these outcomes under risk-stratified screening in comparison to routine breast cancer screening. These include the BC-Predict project in the UK [12], Perspective in Canada [13], and two controlled randomised trial: the Wisdom study in the US [14], and the MyPeBS study (“My Personal Breast Screening”) in Europe and Israel.

The MyPeBS study^2^ is an ongoing randomised controlled trial currently running in six countries (Italy, France, Israel, the UK, Belgium, and Spain) that is testing whether a risk-stratified screening strategy is non-inferior, or eventually better at reducing incidence of advanced breast cancer (i.e. cancers diagnosed at stage 2 or higher), than standard age-based screening. Women from the general population aged 40 to 70 are eligible if they live in a participating area from one of the six participating countries and have never had breast cancer or a high breast cancer risk condition. Participants are randomised 1:1 between the standard arm and the risk-based arm. In the standard arm, women are screened for breast cancer according to the current national guidelines and procedures (bi-yearly or tri-yearly mammogram and/or tomosynthesis, with ultrasound in case of dense breast, starting at age 45–50, up to age 69–74 depending on countries). For the women in the risk-based arm, screening frequency and method depend on their individual 5-year predicted risk of invasive breast cancer, which is estimated at study entry. Risk stratification is done using validated clinical risk scores including a polygenic risk score performed on DNA extracted from a saliva sample and comprising 313 relevant polymorphisms, adjusted for national breast cancer incidence [15]. The primary endpoint (incidence of stage 2 + breast cancer) is measured after four years, at the end of follow-up. Secondary endpoints include false negative and false positive findings, over diagnosis, cost-effectiveness, long-term breast cancer specific mortality, and the present patient-reported data and outcomes.

This study is relevant to address the relative impact of risk-stratified screening for several reasons. First, it is a very large study, with 85,000 women to be randomised. Second, each of the countries in the MyPeBS study have a routine screening programme in which the study is inserted, and against which any additional benefits and harms of risk-stratified screening can be readily compared. Third, it takes place across six different countries with differing screening programmes, healthcare organisations, cultures and ethnic minority populations. Given this, any comparisons of the two approaches to screening will take into account these background factors, to allow the conclusions to be generalisable across countries, or to flag up where caution is needed in making generalisations.

If they were to be implemented on a population scale, risk-stratified breast screening programmes would have to adhere to gold standards of the Wilson and Jungner criteria [16] and additional criteria [17]. In particular, they should ensure that “all components of the screening program be clinically, socially and ethically acceptable to screening participants, health professionals and society” and that there are “effective methods for providing screening participants with informed choice, promoting their autonomy and protecting their rights” [18, 19]. In addition, specific challenges raised by risk stratification need to be addressed, such as the shift in the focus of screening. Indeed, from the practice of diagnosis that aims at detecting the presence of a tumour, it evolves in a broader programme that incorporates risk assessment of developing that cancer in the future [20, 21]. This shift might affect individuals (e.g., anxiety, misunderstanding) but also society (overestimation of cancer risk in the population, stigmatisation and discrimination according to level of risk or non-participation to the screening programme). With these issues in mind, a specific work package within the MyPeBS project aims to examine the ethical, psychological and socio-economic impact of the new screening proposition. This paper describes the research protocol of this work package, including justification of its specific objectives. Objectives and corresponding analytical tools are summarised in Appendix 2.

### Objectives

We aim to compare women in the risk-stratified arm and in the standard arm of MyPeBS, on the following issues: (1) anxiety and cancer worry; (2) understanding of breast cancer screening strategy and information seeking behaviour; (3) socio-demographic and economic characteristics and quality of life; (4) risk perception and intention to change behaviour; (5) acceptability and satisfaction of the trial.The first objective of the research is to assess the emotional impact of risk communication on women. Amongst the potential harms of risk-stratified screening are undue increases in general anxiety or distress related to cancer. The results from a previous study assessing effects of breast cancer risk-stratification found little evidence for elevated distress, although risk information was communicated approximately three years after information on risk factors was elicited from participants [22]. The present study will assess if increased distress is a harm of risk-stratified breast cancer screening, by comparing, at one year, the changes from baseline in levels of general anxiety and cancer-specific worry between women in the risk-stratified arm and women in the standard arm.The second objective aims to assess women’s comprehension of the information provided within MyPeBS, and their willingness to search for further information. One particular aim will be to test whether there is a correlation between women’s information comprehension level, information-seeking behaviours and their sociodemographic and socio-economic characteristics. As risk-based approaches rely on information and schedules that are more complex, it is essential that all decisions made in the context of screening programmes are informed and based on sound understanding of the information provided. Therefore, is it important to assess whether individuals have access to sufficient and clear information to decide to participate and to understand the proposed programme.The third objective is to analyse MyPeBS participants' socio-economic and demographic characteristics as well as quality of life, to assess whether they are representative of the social heterogeneity of the participating countries, and whether these characteristics influence screening perceptions, uptake and behaviours, such as compliance with the proposed breast cancer screening programmes. This relates to a more general aim stated in previous research [23] to identify possible means to further universal access to screening programmes regardless of women’s socio-economic status, cultural origin or literacy level.The fourth objective is to assess perception of risk of breast cancer, and perceptions of efficacy and risks of prevention options [24, 25]. Uptake of options that may reduce future risk of aggressive breast cancer, such as increased mammography frequency in women at high risk, healthier eating, or more physical activity, is linked to perceptions of risk of disease and of the benefits of these behaviours in reducing risk [11]. We will also assess to what extent perceptions of risks and benefits predict intentions to attend future screening and intentions to change lifestyle behaviours (healthy eating, physical activity), and whether they predict subsequent uptake of mammography.The fifth objective aims at measuring overall satisfaction with the trial, and the acceptability of the risk-based approach, should it be implemented at a population scale. First, it is necessary to assess if women are satisfied with this new screening proposal, and with the organisation of the clinical trial, whether they are in the risk-stratified arm or in the standard arm. Furthermore, it is critical to collect women’s feedback on the information and communication materials that they receive throughout the trial, in order to anticipate future needs raised by the large-scale implementation of this new strategy.

In addition to the aforementioned issues which will be assessed globally and for each country, one further objective will be to compare the issues between countries. One of the strengths of the MyPeBS trial is the participation of six countries with specificities in terms of recruitment, local organisation of the trial and type of healthcare professionals involved. Adopting a comparative and contextualised perspective when analysing the results on acceptability of the trial, anxiety and cancer worry, understanding and information-seeking behaviours, equity, risk perception and intentions to change behaviour will offer a more nuanced view on the psychological and socio-economic issues at stake with risk-based approaches.

## Methods and design

### Design of the methodology

In order to meet the described objectives, this work package was designed with two complementary methodologies: a quantitative approach with questionnaires administered to each woman participating in MyPeBS, and a qualitative study consisting of 48 semi-structured interviews conducted with women randomised in the risk-stratified arm in France and in the UK. The use of qualitative methods, in addition to quantitative measures, is recommended in guidance on process evaluation [26], as the two kinds of methods have contrasting strengths.

The quantitative questionnaires will provide measures for the previously stated objectives, at various time points during the trial. Qualitative methods will help further investigate perceptions of risk-stratified screening and collect feedback on the trial from the participants. This qualitative work will give insight into how acceptable women found the process of being offered risk-stratified screening, and their experiences of participating in the trial.

The multi-disciplinary structure of the research team (comprised of researchers in psychology, sociology, health economics, and ethics together with epidemiologists, radiologists, geneticists, patients advocates and clinicians) enriched the design of the methodology of this study. The methodology was reviewed and validated by the project’s executive committee and then approved by ethics committees in each participating country. Data collection and processing are compliant with the European General Data Protection Regulation.

### Participants

Women from the general population (no prior breast cancer and not already identified at high risk) aged 40 to 70 are eligible if they live in a participating area from one of the six participating countries. Women are either invited to participate by the organised breast screening programme structures in each participating country or by a healthcare professional, or she can self-volunteer; indeed, information about the study was disseminated in healthcare providers’ premises (private offices, public screening centres, hospitals), in the media, and through health insurances’ newsletters. Candidates who are interested in participating in the trial and who are eligible with respect to the inclusion and exclusion criteria are registered and randomised via an online dedicated web platform (Eonix, Belgium), and receive a unique identification code that ensures anonymity of data treatment. The participants’ informed consent is obtained by the recruiter before any study-related procedures are performed. The first participant was included on 18^th^ July 2019 and inclusion is still ongoing.

For the qualitative substudy, participants who undergo risk-stratified screening in the MyPeBS trial are recruited by letters sent via screening centres in Manchester (UK) and in the regions of Paris and North of France (France). Study in the UK attempts to recruit a range of women from different levels of socio-economic status. Further informed consent is gained by the study researcher before participants take part in the qualitative study.

### Procedure

Psychosocial questionnaires (see Fig. 1) are administered on the web platform to women at different times during the trial, namely at inclusion (baseline), at three months, at one year and at four years (end of trial). Women complete the baseline psycho-social and medical questionnaires before the randomisation process. Both steps are performed by the recruiter during the inclusion visit. For each other stage of the trial, women receive an invitation by email to complete the next questionnaires. Participants are given a one-month window and receive weekly email reminders to complete the three-months form online. At one year and four years, they are given a two-months window and bi-monthly reminders to fill in the forms. The study sponsor (Unicancer) is responsible for data management and ensures quality control, storage and exportation of data for dedicated analyses.

**Fig. 1 Fig1:**
[figure not shown]
Design of MyPeBS and timing of questionnaire administration. *The baseline mammogram can be performed before or after randomization. If participants had a mammogram in the year prior to recruitment, they do not have to do new one. Psycho-social questionnaires: Q1: STAI (state of anxiety), Q2: Lerman cancer worry scale, Q3: Comprehension, Q4: Information-seeking behaviour and health literacy, Q5: Risk perception, Q6: Quality of life (EQ-5D), Q7: Satisfaction, Q8: Socio-demographic and economic status

For the qualitative study, the research team will conduct 48 semi-structured interviews with women in the risk-stratified arm of the trial, both in France (*n* = 24) and in the UK (*n* = 24). The aim is to recruit six women per risk group (low, average, high and very high), in order to reach data saturation for each of those. Recruitment in France will be carried out with the help of Haut-de-France’s and Ile-de-France’s Regional centres for coordinating cancer screening (CRCDC). Recruitment in the UK will be carried out with help from the Manchester University NHS Foundation Trust (MFT). The interviews will provide an in-depth account of women’s views and experiences of the breast cancer screening programme and allow investigation of how healthcare systems and cultural differences affect acceptability of the proposition.

### Sample size justification

The present study is embedded within the main MyPeBS trial, which aims to recruit 85,000 women from six countries, in 2.5 years, and randomise them to receive either usual screening or risk-stratified screening. The sample size for the main MyPeBS study was based on providing sufficient statistical power to detect non-inferiority of risk-stratified screening in progression of participants to stage 2 breast cancer or beyond.

The present consideration of socio-psychological aspects of risk-stratified screening in the MyPeBS trial will involve the recruitment and follow-up of the entire study sample of women in the MyPeBS trial. This will provide very high statistical power for the five main objectives of the present study. For example, as of December 31st, 2021, 22,884 participants have been recruited, and assuming 70% follow-up of the first 22,000 women, the present study will have over 99% power to detect a very small difference (standard mean difference of 0.08) between the two experimental groups.^3^ Thus, the present sample size will provide more than sufficient statistical power for the five main objectives presented in this paper, and allow well-powered comparisons of these variables in each of the six countries (the sixth objective).

## Measures

### Quantitative questionnaires

Among the questionnaires selected, most are validated questionnaires previously used, some of them in different languages. Appropriate licences have been obtained.

Several questionnaires were created to fit this study aims: the comprehension questionnaire, the information seeking-behaviour questionnaire and the satisfaction questionnaires were built according to previously described methodologies [27–29]. When necessary, the questionnaires were translated to English, Italian, French, Spanish, Dutch, Arabic, Hebrew and Russian, which are the languages commonly used in the six countries of the trial. Translation and reverse translation to English were performed by an official sworn translator. The three versions (English, target language and back translation into English) were then proofread by bilingual professionals involved in the MyPeBS trial. A review of the online versions by the professionals involved in MyPeBS allowed for a final adjustment in the wording. The following subsections give more details on methodological aspects of these questionnaires.

#### State-Trait Anxiety Inventory (STAI) (Q1) and Lerman Cancer Worry scales (Q2) (at baseline, three months, one year and four years)

In order to assess if increased distress is a harm of risk-stratified breast cancer screening, the research team will compare the levels of general anxiety and cancer-specific worry between women who receive risk-stratified screening and women who receive standard screening. Cancer-specific worry measures seem to be more sensitive to the effects of receiving risk information than more general measures of anxiety [30, 31]. By contrast, there is evidence that more general measures of anxiety are better linked to diagnoses of psychological disorders [32]. For this reason, we assess both indices of psychological distress, using standardised measures, namely the short form State-Trait Anxiety Inventory (STAI) to assess general state anxiety [33] and the Lerman cancer-worry scale to assess cancer-specific worry [34].

The Lerman Cancer worry scale questionnaire has been used in similar studies evaluating cancer risk assessment and clinical programmes [22, 35]. The STAI short form questionnaire is a validated questionnaire which has been implemented across many studies, including breast cancer risk-stratification research [22]. Both scales have six items with four response options each. Composite scores are then calculated, with score ranges between 4 and 24, with higher scores indicating higher anxiety.

There is also evidence that both general anxiety and cancer-related worry peak shortly after receiving information on cancer risk and then gradually decline [30, 31]. For this reason, we will assess these variables over time and across the six countries, to examine whether there are short-term increases as well as any longer-term effects.

As levels of anxiety might be affected if women have their mammogram the day they fill in those questionnaires, information on whether or not a mammogram is planned on the day of inclusion will be collected.

#### Comprehension questionnaire (Q3) (at baseline, three months, and four years)

Patients' understanding of health information is a key issue in the exercise of their autonomy, and an ethical principle. This is why different texts—including legal, such as informed consent, or deontological, such as the code of medical ethics or the patient's charter—specify that the physician must provide the patient with a clear, fair and appropriate information on his or her health state, and on the investigations and care proposed. Providing information to the patient and ensuring that he or she understands is a necessary, even if not sufficient, condition for informed or shared decision-making to occur, and is a major public health issue, including in the case of breast cancer screening [36–38].

For all of these reasons, we decided to assess the comprehension of the information provided in MyPeBS. A comprehension questionnaire was developed based on our previous studies [27, 39] and on information tools used by investigators during the accrual visits. The questionnaire contains fifteen true/false questions divided into three categories: (i) general information on breast cancer; (ii) information on breast cancer risk; (iii) information on benefits and risks of breast cancer screening. As this questionnaire was developed for use in this specific study, the questionnaire was piloted amongst a set group of individuals: first, with three healthcare professionals to ensure the scientific relevance of the proposed questions, then with ten women aged 40 to 70. This pilot phase was carried out using face-to-face interviews based on an interview guide containing the main items (clarity of questions, length of questionnaire, redundant or missing questions, etc.) and also the "thinking aloud" procedure [40]. The content was analysed, and questionnaires were improved, on the basis of notes taken during these interviews and their recordings [41, 42].

The comprehension questionnaire will be administered to women at three months and four years. In order to test if responses are not due to pure chance, a Q Cochran test will be used to assess this.

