### Analyses

The quantitative analysis plan (see Appendix 1) includes: 1) descriptive statistics (description of categorical and quantitative variables, tests and estimation of confidence intervals); 2) bivariate analyses, subgroups comparisons and analysis of variations in time (baseline, three months, one year and four years), with appropriate tests to assess differences in groups (e.g. chi-square, Fisher and Student, Q Cochran); 3) multivariate regression models (cross-sectional and longitudinal) to model different patient reported outcomes such as comprehension of the information provided, general anxiety or cancer worry, and information-seeking behaviours. The data management and statistical analyses will be performed using Stata (StataCorp LP) and SPSS (IBM Corp). The main endpoint of this study will be measured at the end of the four years of intervention.

The qualitative data will support the interpretation of findings from the quantitative data. It will use framework analysis, a form of thematic analysis that facilitates the handling of large qualitative datasets [53]. It involves examining qualitative data to produce themes that summarise and interpret patterns of results. The analysis will take an explicit comparative approach, to investigate differences between England and France, and will also consider how the level of estimated risk affects reactions to risk-stratified screening and how acceptable the women found this. Coding will continue until the team is satisfied that codes and themes adequately describe and capture the data and that saturation has been achieved. Data will be stored and organised within Nvivo software (QSR International Pty Ltd. Version 12, 2018).

Dissemination of the study results will include the publication of research papers. A more direct feedback to investigators and to participants is planned at various stages of the trial.

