#### c. Bivariate analyses and subgroups comparisons

The bivariate analyses will mainly focus on detecting differences between subgroups (e.g., countries). Before, it will be ensured that each group contains a sufficient number of participants and is adequately powered.

For the qualitative or discrete variables, the significant differences between subgroups will be assessed either by means of the Chi-square test or by Fisher's exact test depending on the conditions of statistical validity (i.e., theoretical number strictly less than 5).

The Cochran Mantel Haentszel test (or Q Cochran) will test for equality of proportions in matched samples. It will be used to test, for instance, how the comprehension level of risk stratified screening varies in time, (i.e., between baseline, three months and four years).

For quantitative variables, significant differences between two subgroups will be detected via Analysis of Covariance (ANCOVA), controlling for baseline levels of those variables, and any other clinical or demographic variables that are not well balanced between subgroups, and hence may have a confounding effect. Initial assumption testing will include the Fischer test, which will be used to verify the hypothesis of equality of variances, and the Shapiro Wilk test, which will be used to verify the hypothesis of normality. In the case of non-normality, non-parametric approaches will be used in sensitivity analyses. In this case, the Wilcoxon or Mann–Whitney test for comparisons between two subgroups and the Kruskal–Wallis test beyond two subgroups will be considered.

The tests will be bilateral with a significance level of 5%. Adjustments for multiple comparisons (Bonferroni correction) do not appear to be required.

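### Cochran's Q is prescribed to show that comprehension answers are not due to chance, but it has no chance benchmark and neither of its outcomes answers that question

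*Protocol article*

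**What the plan says.** The Measures section describes the instrument: "The questionnaire contains fifteen true/false questions divided into three categories". It then gives the check on the answers: "In order to test if responses are not due to pure chance, a Q Cochran test will be used to assess this". It does not say whether Q is to be run across the fifteen items or across the waves, and it states no proportion or score that would represent chance.

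Appendix 1, section c, says what the test does: "The Cochran Mantel Haentszel test (or Q Cochran) will test for equality of proportions in matched samples". Its example is change in comprehension between waves: "It will be used to test, for instance, how the comprehension level of risk stratified screening varies in time". The Analyses section lists Q among the tests for group differences: "with appropriate tests to assess differences in groups (e.g. chi-square, Fisher and Student, Q Cochran". Tests are two-sided at 5%.

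Appendix 1, section b, plans exact binomial 95% confidence intervals for proportions of interest. No comparison with a chance value appears anywhere in the article.

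**The concern.** The purpose given in the Measures section and the hypothesis given in the appendix do not match. Whether answers are better than chance is a question about the level of the proportions correct. Q asks whether those proportions are equal to one another, at any level.

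This is a test named for a job it cannot do, not a detail left for a later document. The comprehension questionnaire was newly built and was piloted with three professionals and ten women. The chance check is the only statistical check on its answers that the article describes. The article also treats understanding as a necessary condition of informed decision-making. If Q is run as written, a significant result is likely to be reported as evidence that women were not guessing, and it would not show that.

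**Working it through.** **Inputs from the article.** Fifteen true/false items; two-sided 5% level; about 15,400 women followed up (70% of 22,000, from the sample size section).

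**Assumptions, not in the article.** There is no 'don't know' option, so chance is 0.5 per item. Answers are independent within a woman. Eight items are keyed 'true' and seven 'false'. The response lean and the knowledge levels are illustrative.

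The plan gives no figure on this point to reproduce.

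**1. The statistic.** For k items, item totals C_j, woman totals R_i and grand total N:

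Q = (k − 1)[k ΣC_j² − N²] / [kN − ΣR_i²], referred to chi-square on k − 1 degrees of freedom.

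The null is p_1 = … = p_k. The value 0.5 does not appear.

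**2. Simulated rejection rates across 15 items at 5%.** The first column used 1,000 women and 2,000 replicates; the second used 2,000 women and 1,000 replicates.

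| Truth | 1,000 women | 2,000 women |
|---|---|---|
| All guess, 50% correct | 5.7% | 5.7% |
| All items 90% correct | 4.3% | 3.8% |
| All items 20% correct (misinformed) | 6.2% | 6.7% |
| Guessing with a lean: 55% on 8 items, 45% on 7 | 100% | 100% |
| Knowledge from 70% to 95% by item | 100% | not run |

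A lean of only 52/48 gave 99.6% with 2,000 women. A lean of 51/49 gave 100% with 15,400 women (200 replicates).

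**3. Why a small spread is enough.** The non-centrality of Q is about n Σ(p_j − p̄)² / v, where v is the mean within-woman variance.
- Lean of 55/45: p̄ = (8 × 0.55 + 7 × 0.45)/15 = 0.5033 and Σ(p_j − p̄)² = 8 × 0.0467² + 7 × 0.0533² = 0.0373. With v ≈ 0.250 and n = 1,000, this is about 149. The 5% critical value on 14 degrees of freedom is 23.7.
- Items spread evenly from 88% to 92%: Σ(p_j − p̄)² = (0.04/14)² × 280 = 0.00229. With v ≈ 0.090 and n = 2,000, this is about 51. In simulation Q rejected in 300 of 300 samples.

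**4. Across three waves instead.** Constant guessing at 0.5 rejected in 4.8%, and constant knowledge at 0.9 in 5.7%. Knowledge falling from 0.90 to 0.85 to 0.80 rejected in 100%. Q picks up change, not chance.

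**5. A chance benchmark.** For one woman guessing, P(12 or more of 15) = (455 + 105 + 15 + 1)/32,768 = 576/32,768 = 1.76%, and P(11 or more) = 5.9%. A woman who knows each item with probability 0.9 reaches 12 with probability 94.4%.

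**6. Does the benchmark survive a response lean?**
- Single items against 0.5 do not. At 55% and 2,000 women, z = 0.05/√(0.25/2,000) = 4.5 with no knowledge at all.
- The mean score against 7.5 does not. The mean is 8 × 0.55 + 7 × 0.45 = 7.55. At 15,400 women, z = 0.05/√(15 × 0.2475/15,400) = 3.2.
- The share scoring 12 or more hardly moves. Summing Binomial(8, 0.55) and Binomial(7, 0.45) gives 1.82%; with 60/40 it is 1.79%.
- The average of the true-keyed and false-keyed proportions does not move. If a guessing woman answers 'true' with probability t, it is [t + (1 − t)]/2 = 0.5 for any t.

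**The case against.** Four points can be made for the plan.

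First, if every woman guessed independently at exactly 0.5 on every item, Q's null would be true, so a rejection is some evidence against guessing. This stands, but only for that narrow model. A rejection fits guessing with a slight lean equally well, and a non-rejection fits uniform knowledge. A reader might infer that Q carries no information about guessing at all; that goes too far.

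Second, a reader might infer that the test could label excellent understanding as chance. That needs all fifteen items to be almost equally difficult, and a spread of 88% to 92% already produced rejection in every simulated sample. With items from three content categories, near-equal difficulty is unlikely. The realistic failure is that Q nearly always rejects and says nothing.

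Third, a reader might infer that the comprehension results or the trial's conclusions are compromised. The documents do not support this. Objective 2 is analysed by arm comparisons, correlations and regression models, none of which uses the Q result. No exclusion, scoring rule or endpoint depends on it.

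Fourth, the exact binomial intervals already planned would let a reader compare each item with 50%. This helps, but the article does not link them to the chance question, and a response lean can move a single item away from 0.5.

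**Conclusion.** The concern holds in a limited form. The Measures section assigns Cochran's Q a purpose that the article's own definition of the test does not serve. Uniform guessing, uniform knowledge and uniform misinformation all reject at about the nominal 5%. Unequal item difficulty or a small response lean rejects almost always, at sample sizes well below this trial's. Neither outcome shows whether answers exceed chance.

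Severity is moderate. The fault is confined to the check on the comprehension measure. The use of Q in the appendix for change over time in a binary item is sound.

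That Q lacks a chance benchmark needs no assumption. The rejection rates rest on independent answers and the illustrative proportions above. The 0.5 and 1.76% benchmarks rest on a true/false format without a 'don't know' option, which the article neither confirms nor excludes.

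**What to change.** Replace the sentence in the comprehension questionnaire section with a comparison against a stated chance benchmark, by arm and wave:

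- Compare the share of women scoring 12 or more of 15 with the 1.76% expected from guessing.
- Compare the average of the proportions correct on true-keyed and on false-keyed items with 0.5.
- Report item percentages with the exact binomial 95% intervals already planned, descriptively and not as stand-alone proof of knowledge.
- State whether a 'don't know' option exists. If it does, score it as not correct or adapt the benchmark.
- Keep Cochran's Q only for change over time in a binary item.

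The cost is one amended sentence and a matching line in the analysis plan. No new data are needed.
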